### 2.2. Settings and Study Participants

The study will be conducted at mental health and addiction (MHA) outpatient and inpatient services, including community mental health and addiction programs (CMHAPs), specialty programs (SPs), addiction programs (APs), emergency departments (EDs), and psychiatric inpatient units (PIUs), across the province of Nova Scotia, Canada. The recently launched Day Hospital and the Transcultural Mental Health Program, as well as the Rapid Access and Stabilization Program that is expected to be initiated, will be part of the study, totalling 46 study sites. New patients (i.e., first-time users) of MHA outpatient programs and patients being discharged from MHA inpatient facilities (i.e., at most one week prior to their expected discharge date) will be eligible for the study. Additionally, they must be 18 years old or older, have a phone capable of receiving text messages (no data plan is required), be able to read English, and provide written consent. Patients will be disqualified if they are unable to read text messages from a mobile device or are unwilling or unable to grant permission to participate in the trial.

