### 2.4. Study Procedures

#### 2.4.1. Consent Process

Patients from all study sites will be initially provided with information about the study by someone from their circle of care. A research team member will facilitate the study presentation, consent process, and study enrolment on the day of the patient’s enrolment in the MHA outpatient program or within a week before their expected discharge date from the inpatient units. A REDCap-based electronic consent form (e-Consent) will be used to obtain consent. The person obtaining consent will gain access to the information leaflet about the study and the e-Consent by pointing a mobile device camera (tablet supplied by the study or patient’s mobile phone) to a QR Code, which will open the form link. During the informed consent process, patients will receive detailed information about the study’s goal and procedures, risks and benefits, and participation alternatives. They can choose whether or not to participate in the RCT and/or the qualitative sub-study by providing consent or not. Participants will be advised about the voluntary nature of the study and that they may withdraw from the study at any time they want without giving a reason. A digital copy of the information leaflet will be sent to the participant’s email address at the completion of the consent procedure.

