#### 2.4.2. Baseline Assessment

After providing consent, all subjects will be asked to complete an online baseline survey. The baseline survey includes sociodemographic information and self-completed validated scales designed to assess the patient’s mental health outcomes. During the baseline assessment, participants will be given the option of selecting the message bank from which they want to receive text messages based on their needs (i.e., depression, anxiety, bipolar disorder, etc.). In addition to that, one clinician-rated scale, which evaluates suicidal risk, will be completed by a trained research team member in person or over the phone. The average time for completing the baseline survey is 10 min.

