#### 2.4.4. Follow-Up Assessment

Participants in both study arms (intervention and control) will receive a link to the follow-up self-completed online surveys through SMS and be asked to complete them at 6 weeks and 3, 6, and 12 months after enrolment in the study. The same clinician-rated scales completed at enrolment will be completed over the phone by a trained research team member. A monitoring compliance strategy will be put into practice (a reminder text message after two days and then phone calls from the research team) in order to mitigate the loss of follow-up and improve patient compliance.

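### Eligibility waives a data plan, but the only stated follow-up route for RAS and WHO-5 is a web link sent by SMS, so participants without ready web access are at raised risk of missing primary outcomes

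*Protocol article*

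**What the plan says.** Section 2.2 sets the device criterion: participants must "have a phone capable of receiving text messages (no data plan is required"). It states no internet requirement.

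Section 2.6 names RAS and WHO-5 as the primary clinical outcome measures. The footnote to Table 1 marks both as online and patient-completed, with collection at baseline, 6 weeks, and 3, 6 and 12 months.

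Section 2.4.4 gives the follow-up route. Participants in both arms "will receive a link to the follow-up self-completed online surveys through SMS". For the clinician-rated assessment it says: "The same clinician-rated scales completed at enrolment will be completed over the phone by a trained research team member". Non-response is followed up by "a reminder text message after two days and then phone calls from the research team".

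At entry, Section 2.4.1 lets the leaflet and e-Consent be opened by pointing a device ("tablet supplied by the study or patient’s mobile phone) to a QR Code". A copy of the leaflet "will be sent to the participant’s email address at the completion of the consent procedure". Section 2.4.2 then says that "all subjects will be asked to complete an online baseline survey" and names no device.

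Section 2.3 requires 262 completed responses at each time point, takes about 20% as the maximum completion rate for online surveys delivered by text, and plans at least 1500 participants.

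**The concern.** The device criterion follows from the intervention, which is plain SMS. The primary outcome depends on something that criterion does not ask for: the ability to open a web page. Nothing in the stated criteria stops a person with a text-only phone, or one without ready internet access, from being randomised and receiving every message. At each follow-up the primary scales then reach that person as a link they may be unable to open.

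Two things are at stake. First, some primary outcome data may be lost for a reason that is foreseeable and cheap to reduce. Second, people with limited web access may differ from the rest in ways related to outcome, so an estimate driven by those who can open links may not describe everyone the eligibility rule admits. Enrolling more people protects the number of completers but not their make-up. Multiple imputation (Section 2.7) helps with make-up only as far as the imputation model contains the variables that predict missingness, and ability to open a link is an obvious candidate.

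**Working it through.** **Entry against measurement**

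| Step | What is needed | Where stated |
|---|---|---|
| Enter the trial | Phone that receives texts; data plan waived | 2.2 |
| Consent | Study tablet or own phone | 2.4.1 |
| Baseline scales | Online survey, device not stated | 2.4.2 |
| Receive the intervention | SMS only | 2.2, 2.5 |
| RAS, WHO-5 at the 4 follow-ups | Web link sent by SMS | 2.4.4, Table 1 |
| C-SSRS at the 4 follow-ups | Telephone call | 2.4.4, Table 1 |

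The row for RAS and WHO-5 is the only follow-up step that needs the web. It has no stated alternative, although a telephone contact is scheduled at the same four time points for another scale.

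**The plan's own figures (Section 2.3)**

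- Inputs: difference in mean change 10 − 8 = 2; two-sided α = 0.05; power 90%; 5.0 as the measure of spread.
- n per arm = 2 × (1.960 + 1.282)² × 5² / 2² = 131.3, against the stated 131. This match treats 5.0 as a standard deviation. The text calls it a variance, which would give 27 per arm. That is a separate matter; the power figures below use the reading that reproduces 131.
- Total completers needed: 2 × 131 = 262.
- Enrolment needed at 20% completion: 262 / 0.20 = 1310. Planned: at least 1500.
- Expected completers: 1500 × 0.20 = 300. Margin: 300 − 262 = 38.

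**Effect of a share x without web access**

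The protocol does not give x, so the values below are assumptions.

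*Case A: the 20% rate already includes people who cannot open links.* Expected completers stay at 300 and power at about 93%, whatever x is. Only representativeness is affected.

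*Case B: the 20% rate applies only to people with access, and the others return nothing.* Completers = 1500 × (1 − x) × 0.20 = 300 × (1 − x). Enrolment needed = 262 / [0.20 × (1 − x)].

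| x (assumed) | Randomised without access | Completers | Power | Enrolment needed |
|---|---|---|---|---|
| 5% | 75 | 285 | 92% | 1379 |
| 10% | 150 | 270 | 91% | 1456 |
| 20% | 300 | 240 | 87% | 1638 |
| 30% | 450 | 210 | 83% | 1872 |

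Break-even: 300 × (1 − x) = 262 gives x = 1 − 262/300 = 12.7%.

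Case B is the upper end, because it assumes that nobody in the group finds Wi-Fi or another device.

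**The case against.** The strongest reply is that having no data plan is not the same as having no internet. A smartphone without a plan opens a link over Wi-Fi, another device may be at hand, and the leaflet going to an email address implies some online access. This stands. A reader might infer that these participants have no usable route and that their outcomes are missing by construction; the protocol supports only a raised risk.

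A reader might also infer that baseline is completed on a study tablet, so that a text-only phone is never noticed before randomisation. The tablet is mentioned for the leaflet and e-Consent, and the device for the baseline survey is not stated. Tablet use there is plausible but not established.

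It would likewise go too far to say that web access is not recorded, or that imputation cannot recover the group. Section 2.4.2 mentions sociodemographic items without listing them, and Section 2.7 plans an analysis of missingness patterns and several sensitivity analyses. One can say only that the article does not name such an item.

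The reminder text and telephone calls are a fair point, since staff could deal with access problems during them. However, they are described as a way to improve compliance, and nothing says that RAS or WHO-5 is collected in them. Operational detail may sit in a fuller protocol, but the article states both the device waiver and the web-only route, and the two do not fit together.

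Finally, very low completion is already planned for, and the survey route is the same in both arms. Both points hold. The first may leave precision unchanged (Case A) but does not address who responds. The second means that a reader should not infer a built-in difference between arms. Service-use outcomes come from administrative records and are unaffected.

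**Conclusion.** The mismatch is in the text and is worth correcting, but it is modest. Eligibility admits people whose phones may not readily open the only stated follow-up form for RAS and WHO-5. They are at raised risk of missing primary outcomes at all four follow-ups unless they use Wi-Fi or another device. The consequence is avoidable missing data and a narrower population behind the estimate.

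The size cannot be fixed from the protocol. For completer numbers it ranges from no effect, if the 20% rate already covers such people, to loss of the whole 38-completer margin at about 12.7% without access, if it does not. Even at an assumed 20%, power on the plan's own inputs would be about 87%. Against about 1200 expected non-completers (1500 − 300), this is probably a minority cause of missing data, but it is one that can be identified and reduced at little cost.

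**What to change.** 1. Add one baseline item asking whether the participant can open web links on the phone that will receive the texts.
2. For those who cannot, offer a second route through contacts the plan already has: a survey link to the email address used at consent, for those with another device, or RAS and WHO-5 read out during the already scheduled C-SSRS call. Apply the rule identically in both arms and record the mode.
3. Include the access item in the imputation model and report completion by access and by arm.
4. If no second route is offered, restate eligibility as having a phone or other device that can open web links, and limit the conclusion to that population.

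The cost is one question, some longer calls for a minority, and a few lines of protocol text. The downside is mixed survey modes: scales read out by staff may be answered differently from scales completed alone. Recording the mode allows this to be examined, and using the same rule in both arms keeps it from favouring one by design.

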### 2.3. Sample Size Considerations

With a hypothesized difference of 20% in change scores (from baseline to the four-time points) for each of the primary outcome variables of interest (e.g., mean change score of 10 vs. 8), a population variance of 5.0 for the mean change score, a 2-sided significance level (α = 0.05), a power of 90% and an acceptable difference between the sample mean and population mean score for each scale of zero (μ − μ0 = 0), an estimated sample size of 131 participants in each arm of the study would be needed (based on the 6Sigma online script) to detect the projected mean differences in mean change scores between the intervention and control groups [29,30]. Thus, the sample size for the RCT would be 262. Given that the maximum survey completion rate for the online surveys delivered via text message is approximately 20%, in order to achieve 262 completed survey responses at each time point, we plan to enrol at least 1500 participants in the RCT. This recruitment rate is achievable since a related study in Alberta [31] currently has over 500 patients recruited within six months. The sample size for the qualitative component of the study cannot be predetermined. Data saturation is reached across data analysis, ending when no new themes and subthemes emerge. However, based on what the literature suggests [32,33], we anticipate that 25–30 participants may be sufficient for this particular mixed-method study.

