## 2. Materials and Methods

### 2.1. Study Design

This randomized controlled trial (RCT) is a multicenter, longitudinal, prospective, parallel, two-arm, rater-blinded methodology, with an embedded one-phase patient satisfaction qualitative sub-study and an implementation evaluation component. Hence, the study will have two groups (i.e., intervention group (IG) and control group (CG)), to which study participants will be randomized. The randomization process will employ permuted blocks, to ensure balance (1:1) between groups. To ensure allocation concealment, simple random allocation will be performed using a random number generator. The primary outcome measure for this study is transdiagnostic, with recruitment occurring in all mental health clinics and programs across the province, so stratified sampling will not be employed. Research team members working on the randomization and allocation processes will not be involved in the baseline and follow-up assessments. Data analysts will be blinded to treatment group allocation. Study subjects will, however, not be blinded since it is impossible to conceal which experimental condition they will be assigned to.

The qualitative sub-study on patient satisfaction will utilize qualitative descriptive methodology and thematic analysis [27]. We will select a purposive sample of the research participants to attend focus group sessions to uncover patterns or themes in the patient experience and satisfaction with the interventions. Finally, guided by the RE-AIM framework [28], we will evaluate the success of Text4Support implementation by looking at the intervention’s reach, effectiveness, willingness to adopt it, fidelity, and sustainability post-trial.

This protocol has been registered at ClinicalTrials.gov (NCT05411302) and approved by the Research Ethics Board for Nova Scotia Health (REB File#1028174). The trial will be carried out over three years, with 24 months dedicated to recruitment. The intervention will be delivered for 6 months, followed by an observation period of 12 months for each participant. The study flow diagram is represented in Figure 1.

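### The stated variance of 5.0, 131 per arm and 90% power do not agree; a standard deviation of 5.0 would very probably reconcile them

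*Protocol article*

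**What the plan says.** The calculation is in section 2.3 of the protocol article (Sample Size Considerations). Its inputs are:

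- for the variability, "a population variance of 5.0 for the mean change score";
- for the effect, an expected 20% difference in change scores on each primary variable, illustrated as "e.g., mean change score of 10 vs. 8";
- for the error rates, two-sided alpha 0.05 and 90% power;
- as a further entry, "an acceptable difference between the sample mean and population mean score for each scale of zero (μ − μ0 = 0").

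From these the section states that "an estimated sample size of 131 participants in each arm of the study would be needed", with the figure attributed to an online script. It goes on: "Thus, the sample size for the RCT would be 262". Enrolment is then raised to at least 1500 because "the maximum survey completion rate for the online surveys delivered via text message is approximately 20" per cent. Section 2.1 sets permuted-block randomisation "to ensure balance (1:1) between groups". The article gives no standard deviation and no second variance, and it shows no calculator input or output.

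**The concern.** A variance of 5.0 means a standard deviation of about 2.24, so 2 points would be a very large standardised effect. An effect of that size needs far fewer than 131 per arm at 90% power. One of the printed quantities must be wrong.

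This matters because the sentence is the only basis given for 131, for 262 and, through the completion rate, for the enrolment target. The raw target of 2 points is clear. What a reader cannot tell is the assumed variability, and hence the standardised effect the trial was sized for. Anyone who later compares the observed spread of change scores with the planning value would be using a benchmark that may be five times too small on the variance scale.

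**Working it through.** **Inputs.** Difference 2 (10 − 8), variance 5.0, two-sided alpha 0.05 and power 90% come from section 2.3. The 1:1 allocation comes from section 2.1.

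**Formula.** For two independent means under the normal approximation, n per arm = 2 × (z₀.₉₇₅ + z₀.₉₀)² × variance / difference². Here (1.960 + 1.2816)² = 10.507.

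**1. Inputs as printed.** 2 × 10.507 × 5.0 / 4 = 26.3, so 27 per arm. The t-test version gives 27.3, so 28. The total is 54 to 56, not 262.

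**2. Can another convention rescue variance 5.0?** With the difference held at 2:

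| Variant | n per arm |
|---|---|
| Variance doubled to 10 | 52.5 |
| One-sample formula, variance 5.0 | 13.1 |
| Variance 5.0, 95% power, alpha 0.00625 two-sided | 48 |
| Variance 10, 95% power, alpha 0.00625 two-sided | 96 |

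The last row is the largest value found when sidedness, power (80, 90, 95%) and alpha (0.05, 0.025, 0.0125, 0.00625) were all varied. None comes near 131.

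**3. Standard deviation 5.0, all else unchanged.** 2 × 10.507 × 25 / 4 = 131.3 per arm, which is 131 when truncated or rounded to the nearest integer. The t-test version gives 132.3.

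**4. Back-solving from 131.** Variance = 131 × 4 / (2 × 10.507) = 24.93, so the standard deviation is 4.99.

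**5. Power and detectable difference at 131 per arm.**

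- Variance 5.0: power for 2 points exceeds 99.99%. The difference detectable with 90% power is √(2 × 5.0 × 10.507 / 131) = 0.90 points.
- Standard deviation 5.0: power for 2 points is 89.9% (normal) or 89.7% (t-test).

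**6. Standardised effect.** 2 / √5.0 = 0.89 as printed; 2 / 5.0 = 0.40 with a standard deviation of 5.

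**7. Enrolment at 20% completion.** 262 / 0.20 = 1310. With 132 per arm, 264 / 0.20 = 1320. With 27 per arm, 54 / 0.20 = 270. The plan of 1500 gives 1500 × 0.20 = 300 completers.

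**The case against.** The strongest reply is that the cause cannot be proved. The script's input is not shown, and 10 vs 8 is offered only as an example of a 20% difference. If the difference is left free, variance 5.0 with about 0.90 points also gives 131 per arm. A reader might infer that 131 can only have come from a standard deviation of 5; the documents do not support that certainty. This part of the reply stands. The competing reading is much less likely, because 10 vs 8 is the only pair printed and a standard deviation of 5 reproduces 131 with no other change.

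A second reply is that nothing operational follows. That also stands. With a standard deviation of 5 the stated n has almost exactly the claimed power; with variance 5.0 it has more than enough. A reader taking the text literally might infer that the trial enrols about five times too many patients (1310 against 270). That would follow only if variance 5.0 was truly meant, which the back-calculation makes improbable.

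The rounding from 131.3 to 131 costs at most 0.3 percentage points of power and is minor. So is the clause on the difference between sample and population mean: it has no role in a two-sample comparison, but it may simply record a field of the script.

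None of this answers the main point. As printed, the variance, the n and the 90% power cannot all be true with a difference of 2.

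**Conclusion.** The point holds as an inconsistency among stated inputs. A difference of 2 with variance 5.0, two-sided alpha 0.05, 90% power and 1:1 allocation requires 27 to 28 per arm. The stated 131 is about five times that, which is the ratio of variance 25 to variance 5. A mislabelled standard deviation is the very probable explanation, but it remains an inference until the sponsor checks the script input.

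The result rests on a standard two-sample comparison of means and on taking the printed example of 2 points as the design difference. The article gives no source for 5, either as a variance or as a standard deviation, on either primary scale, so this check says nothing about whether the value is realistic. The error affects how the design is reported and understood. It does not show the trial to be under-sized, and it gives no reason to alter enrolment.

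**What to change.** Check the value entered in the online script, then correct the sentence in section 2.3 accordingly.

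- **If a standard deviation of 5 was entered:** replace the variance statement with a standard deviation of 5.0 (variance 25) and give the standardised effect as 0.40. Then either state 132 per arm, which rounds up 131.3 for a full 90% under the normal approximation (133 by t-test, from 132.3), or keep 131 and state the power as 89.7%.
- **If variance 5.0 was truly meant:** restate the required n as about 27 to 28 per arm, or keep 131 and state the detectable difference as about 0.90 points.

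In either case, say briefly where the variability figure comes from for each primary scale. The clause on the sample and population mean can be dropped or explained at the same time.

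The cost is one sentence and a look at the calculation record. The enrolment target of 1500 stays: its 300 expected completers exceed 262, 264 (132 per arm) and 266 (133 per arm).

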### 2.4. Study Procedures

#### 2.4.1. Consent Process

Patients from all study sites will be initially provided with information about the study by someone from their circle of care. A research team member will facilitate the study presentation, consent process, and study enrolment on the day of the patient’s enrolment in the MHA outpatient program or within a week before their expected discharge date from the inpatient units. A REDCap-based electronic consent form (e-Consent) will be used to obtain consent. The person obtaining consent will gain access to the information leaflet about the study and the e-Consent by pointing a mobile device camera (tablet supplied by the study or patient’s mobile phone) to a QR Code, which will open the form link. During the informed consent process, patients will receive detailed information about the study’s goal and procedures, risks and benefits, and participation alternatives. They can choose whether or not to participate in the RCT and/or the qualitative sub-study by providing consent or not. Participants will be advised about the voluntary nature of the study and that they may withdraw from the study at any time they want without giving a reason. A digital copy of the information leaflet will be sent to the participant’s email address at the completion of the consent procedure.

